#### **5.5.5.b Treatment of Ipilimumab-Related Isolated Drug Fever**

In the event of isolated drug fever, the investigator must use clinical judgment to determine if the fever is related to the ipilimumab or to an infectious etiology. If a patient experiences isolated drug fever, for the next dose, pre-treatment with acetaminophen or non-steroidal anti-inflammatory agent (investigator discretion) should be instituted and a repeated antipyretic dose at 6 and 12 hours after ipilimumab infusion, should be administered. The infusion rate will remain unchanged for future doses. If a patient experiences recurrent isolated drug fever following premedication and post dosing with an appropriate antipyretic, the infusion rate for subsequent dosing should be decreased to 50% of the previous rate. If fever recurs following infusion rate change, the investigator should assess the patient's level of discomfort with the event and use clinical judgment to determine if the patient should receive further ipilimumab.

**5.5.5.c Liver Function Tests (LFT) Assessments Required Prior to Administration of ipilimumab**

Liver function tests (AST, ALT, T. bilirubin) will be evaluated for every subject prior to administration of ipilimumab. Blood samples must be collected and analyzed at local or central labs within 3 days prior to dosing. LFT results must be reviewed by the principal investigator (or designee) to meet dosing criteria specifications:  $\leq 2.5 \times \text{ULN}$  for AST, ALT and  $\leq 1.5 \times \text{ULN}$  for T. bilirubin unless liver metastases are present in which case  $\text{LFT} \leq 5 \times \text{ULN}$  for AST, ALT and T. bilirubin  $\leq 3.0 \times \text{ULN}$  prior to dosing.

If, during the course of treatment abnormal LFT values are detected, the subject must be managed using the hepatotoxicity algorithm section of the ipilimumab Investigators.

**5.6 Prohibited and Restricted Therapies During the Study****5.6.1 Prohibited Therapies**

Patients in this study may not use vaccines for the treatment of cancer or prevention of disease (including those for common medical conditions) for up to one month pre and post dosing with ipilimumab. Concomitant systemic or local anti-cancer medications or treatments are prohibited in this study while receiving ipilimumab treatments.

Patients may not use any of the following therapies during the study:

- Any non-study anti-cancer agent (investigational or non-investigational)
- Any other investigational agents
- Any other (non-CA184024 related) CTLA-4 inhibitors or agonists
- CD137 agonists
- Immunosuppressive agents
- Chronic systemic corticosteroids
- Any non-oncology vaccine therapies used for the prevention of infectious diseases (for up to 30 days prior to or after any dose of study drug).

**5.6.2 Restricted Therapies**

“Not applicable.”

## **6. STUDY PROCEDURES AND OBSERVATIONS**

### **6.1. Procedures by Visit**

#### **6.1.1. Study Procedures by Visit and Treatment Cycle**

Note that results of all safety laboratory tests (that is, all chemistry and all hematology results) must be obtained and reviewed before ipilimumab administration, as applicable. All laboratory results must be within the established range before ipilimumab is administered. All induction period laboratory samples must be collected within a window of up to 3 days before administration of ipilimumab. Laboratory evaluations using a local laboratory must be performed and the result examined by the investigator before administration of each dose of ipilimumab.

The disease will be assessed at baseline, after 12 weeks and for patients with stable disease or better responses, thereafter every 12 weeks in the absence of PD to a maximum of one year. Response evaluation will be done according to RECIST and immune-related response criteria (1).

All patients who prematurely discontinue treatment due to a drug-related adverse event prior to Week 12 (in the absence of disease progression) will return for all study visits and procedures including Week 12 and, if appropriate, further re-staging assessments until disease progression is observed.

- Subjects who are no longer receiving ipilimumab because of unacceptable toxicity (refractory Grade  $\geq 3$  irAEs) or due to investigator judgment are followed with tumour assessment until ir PD. Efficacy assessments for these subjects during follow-up are as per the standard of care. Date of death is recorded.
- Subjects who discontinue ipilimumab treatments are followed with tumour assessment until ir PD and should be followed until death or the closure of the study (whichever is first).
- Subjects who are no longer receiving ipilimumab because of progression and who have switched to alternative treatment are not followed formally except to record the date of death.

Any patient with documented progression at any scheduled re-staging visit who is not eligible for re-induction treatment will undergo no further re-staging visits and enters the Follow up phase (FU phase).

At the time of closure of the study (LPFV+12 months), it will be ensured that survival status (alive/dead and date) has been collected for each subject for each subject's full follow-up period (i.e: for 1 year from the subject's first treatment dose).

#### **6.1.1.1. Screening/Baseline Visit**

At the screening/baseline visit, the patient will consent to the study and eligibility will be determined according to the inclusion/exclusion criteria as detailed in Section 4. Patients must meet all inclusion criteria and none of the exclusion criteria to be considered eligible. In addition, a full medical history, prior and ongoing antineoplastic therapies, concurrent medications, and demographic information will be collected. Baseline CT/MRI and photographic imaging will take place at this visit. The following tests and examinations must be performed and the eligibility criteria satisfied before treatment may begin:

**All patients participating in this clinical study with ipilimumab their TSH level must be assessed at baseline and before each dose and the TSH level be available to the investigator prior to the administration of the dose. The assessment of TSH is mandatory prior each treatment.**

- Histologic diagnosis of malignant melanoma, B-RAF status of tumor biopsy
- Demographics and medical history
- Measurements of weight, height, temperature, pulse, respiratory rate, and resting systolic and diastolic blood pressure
- Complete physical examination
- ECOG Performance Status
- Current medications
- Baseline signs and symptoms
- Urine pregnancy test for WOCBP.
- Electrocardiogram (ECG): Patients with an existing myocarditis are excluded from this study.
- Baseline MRT/CT brain and MRT/CT chest/abdomen/pelvis scan was performed. The images can be accepted if obtained 6 weeks before initiation of ipilimumab
- Clinical laboratory tests:
  - Hematology: hemoglobin, CBC counts with differential (including absolute lymphocyte count) and direct platelet count.
  - Serum Chemistry: albumin, CRP, SGOT (AST)/SGPT (ALT), bilirubin (direct and total), creatinine, lactate dehydrogenase (LDH), lipase, electrolytes (including sodium, potassium, chloride, and bicarbonate) TSH, Free T4, S-100
  - Urinalysis (urine dipstick for protein)
- B-Raf Mutational Status and Microtissue Array:

Currently nothing is known whether response to ipilimumab might also be modulated by b-raf mutational status. Therefore Formalin Fixed Paraffin Embedded (FFPE) tissue is requested from every patient. FFPEs blocks from histologically confirmed cutaneous melanoma such as. Primary tumor or subsequent metastases such as lymph node etc. will be eligible.

DNA will be extracted and analysed for B-raf V600E mutational status by PCR. Furthermore, tissue micro arrays (TMAs) will be constructed to investigate tumor microenvironment and tumor infiltrating immune cells

#### **6.1.1.2. Treatment Visits** (Visits 2 through 5 + End of treatment visit)

Tumor assessments should be performed until disease progression is observed, both for induction and re-induction.

#### **Induction Treatment**

Subjects are required to have blood collected and chemistry labs analyzed up to 72 hours prior to each dose of ipilimumab. Investigators or an assigned medical professional must review liver function tests from the predosing labs and ensure the results meet dosing requirements prior to authorizing administration of each dose of ipilimumab.

During this treatment phase, the following procedures will be performed within +/- 7 days of each scheduled visit:

- Vital sign measurements will include weight, temperature, pulse, and resting systolic and diastolic blood pressure. Vital sign measurements of pulse, and systolic and diastolic blood pressure will be collected every 30 minutes for the duration of the ipilimumab, 1 hour following the completion of the infusion, and routinely unless otherwise indicated
- Physical examination
- ECOG Performance Status
- ECG: Patients with evident of myocarditis are excluded. Patients with suspicion of myocarditis (e.g. dyspnoea, functional insufficiency etc.) ECG examinations have to be performed before each treatment.
- Clinical laboratory tests (as outlined in the screening phase) must be analyzed within 3 days prior to dosing (results reviewed prior to study drug administration):

All patients participating in this clinical study with ipilimumab their TSH level must be assessed at baseline and before each dose and the TSH level be available to the investigator prior to the administration of the dose. **The assessment of TSH is mandatory prior each treatment.** If a subject has thyroid dysfunction and concomitant symptoms (i.e. fatigue), the subject should be

monitored more frequently and be treated as per standard medical practice. The management algorithm for endocrine abnormalities is available on page 59 (appendix 10-15).

- Hematology
- Serum chemistry
- TSH, Free T4 (Visits 2 -5 [prior to study drug administration])
- LDH, S-100 (Visit 2, 3, 5)
- Urinalysis (urine dipstick for protein)
- Assessment of signs and symptoms
- Urine pregnancy test for WOCBP (not at end of treatment visit)
- Concomitant medications
- Adverse event assessment

### ***Re-induction Treatment***

For all subjects, during the Re-Induction Phase, the following procedures must be performed within 3 days of each scheduled visit and recorded in the CRF at the scheduled visit:

- Urine pregnancy test for WOCBP
- Vital sign measurements will include weight, temperature, pulse, and resting systolic and diastolic blood pressure. Vital sign measurements of pulse, and systolic and diastolic blood pressure will be collected every 30 minutes for the duration of the ipilimumab, 1 hour following the completion of the infusion, and routinely unless otherwise indicated.
- Physical examination
- ECOG Performance Status
- ECG (baseline and week 12): Patients with evident of myocarditis are excluded. Patients with suspicion of myocarditis (e.g. dyspnoea, functional insufficiency etc) ECG examinations have to be performed before each treatment
- Clinical laboratory tests (as outlined in the screening phase) (taken and results reviewed prior to study drug administration):

All patients participating in this clinical study with ipilimumab their TSH level must be assessed at baseline and before each dose and the TSH level be available to the investigator prior to the administration of the dose. **The assessment of TSH is mandatory prior each treatment.** If a subject has thyroid dysfunction and concomitant symptoms (i.e. fatigue), the subject should be monitored more frequently and be treated as per standard medical practice. The management algorithm for endocrine abnormalities is available on page 59 (appendix 10-15).

- Hematology
- Serum chemistry
- TSH, Free T4 (Visits 2 and 4 [prior to study drug administration])
- LDH, S-100 (Visit 2, 3, 5)
- Urinalysis (urine dipstick for protein)

- Assessment of signs and symptoms
- Concomitant medications
- Adverse event assessment

All patients who prematurely discontinue treatment due to a drug-related adverse event prior to Week 12 (in the absence of disease progression) will return for all study visits and procedures including Week 12 and, if appropriate, further re-staging assessments until disease progression is observed.

#### **6.1.1.3. Restaging-Visits**

Restaging-visits will be invited for all patients in a 12-week interval who have potentially benefitted from treatment. All patients should undergo radiographic tumor assessments every 12 weeks until disease progression is observed, both for induction and re-induction. Restaging-visits will be performed for each subject during a maximum of 1 year following first treatment dose. The End of Study visit should be performed when tumor follow-up on the patient will no longer continue, regardless of whether the patient progressed or not.

The following procedures will be performed within of each scheduled restaging

- Measurements of vital signs (resting systolic and diastolic blood pressure, pulse, respiratory rate, and temperature) and weight
  - Physical examination
  - ECOG Performance Status
  - ECG at week 12 only
  - Clinical laboratory tests
    - Hematology
    - Serum chemistry
    - TSH, Free T4
  - LDH, S-100 (Visit 5/ week 12)
    - Urinalysis (urine dipstick for protein)
  - Assessment of signs and symptoms
  - Concomitant medications
  - Adverse event assessment.
- Study Completion or Early Discontinuation Visit

At the time of study early withdrawal, the reason for early withdrawal and any new or continuing adverse events should be documented.

**6.1.1.4. End of Treatment Visit**

The end of treatment visit will be performed 10 weeks after last administration of study therapy. The following procedures will be performed during end of treatment visit:

- Measurements of vital signs (resting systolic and diastolic blood pressure, pulse, respiratory rate, and temperature) and weight
- Physical examination
- ECOG Performance Status
- Clinical laboratory tests
  - Hematology
  - Serum chemistry
  - TSH, Free T4
  - Urinalysis (urine dipstick for protein)
- Assessment of signs and symptoms

**6.1.1.5. FU-Phase**

Patients who have progressed initially and were not eligible for re-induction are followed for survival only on a regular basis e.g. 3 months intervals by phone until death, the trial ends or the patient becomes lost-to-follow-up (LTFU). At the time of closure of the study (LPFV+12 months), it will be ensured that survival status (alive/dead and date) has been collected for each subject for each subject's full follow-up period (i.e: for 1 year from the subject's first treatment dose).

## 6.2. Safety Assessments

All patients who receive at least one dose of ipilimumab will be considered evaluable for safety parameters. Additionally, any occurrence of nonserious or SAE from time of consent forward, up to and including follow-up visits, will be reported. See Section 8: Adverse Event Reporting.

Safety will be evaluated for all treated patients using the National Cancer Institute (NCI) Common Terminology Criteria for Adverse Events (CTCAE), Version 4.0 ([http://www.acrin.org/Portals/0/Administration/Regulatory/CTCAE\\_4.02\\_2009-09-15\\_QuickReference\\_5x7.pdf](http://www.acrin.org/Portals/0/Administration/Regulatory/CTCAE_4.02_2009-09-15_QuickReference_5x7.pdf)). Safety assessments will be based on medical review of adverse event reports and the results of vital sign measurements, physical examinations, and clinical laboratory tests.

Appendix 10 to 15 presents algorithm for safety and provides recommendations for immunerelated adverse events. The algorithm should help to inform and enhance patient care and reduce the risk of immunerelated AEs and to initiate therapy and minimize complications.

Immunerelated AEs are generally manageable using symptomatic or immunosuppressive therapy as recommended through detailed diagnosis and management guidelines as described in the investigators' Brochure (IB version no: 13 dated 26-Aug-2010). The management guidelines for general immune-related AEs and ipilimumab-related gastrointestinal toxicities, hepatotoxicity, endocrinopathy and neuropathy are provided in the IB Appendices 6,7,8,9, and 10 respectively. In addition if necessary please contact the study core center.

## 6.3. Stopping Rules

The trial can be prematurely closed or suspended by the sponsor in following cases:

- If  $\geq 50\%$  of treated patients present an AE  $\geq$  grade III which is at least possibly related to ipilimumab
- If  $\geq 20\%$  of treated patients experience an unexpected at least possibly related AE which is not be alleviated or controlled by appropriate treatment and/or systemic steroids and/or infliximab within 14 days after initiation of such therapy
- If any ipilimumab-related death occurred unless also attributed to disease progression

In case of occurrence of any of the above listed situations the accrual will be suspended if appropriate until the sponsor has reviewed the events together with BMS and determined the appropriate course of action which could include the discontinuation of the trial, a protocol amendment or trial continuation as started. No efficacy data will be analyzed at this time point. Patients who are already on treatment will be informed individually if stopping rules apply based on the interim safety analysis. It will be individually decided together with each patient, whether further treatment according to protocol is applied.

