#### **1.3.4c Safety of Ipilimumab Every 3 Weeks for 4 Doses**

As of 31 March 2009, 658 subjects with metastatic refractory melanoma have been enrolled to be treated with 10 mg/kg of ipilimumab every 3 weeks for four doses and followed for at least 12 weeks. The overall rate of irAEs (immune-related adverse event (irAE)), regardless of grade for subjects receiving 10 mg/kg, was 21.9% including 12.9%% with serious gastrointestinal irAEs, 5.1% with hepatic dysfunction and 3.2% with serious endocrinopathy. The most recent Ipilimumab Investigator Brochure (and addenda) should be consulted for the most current details of safety. More than 200 subjects with metastatic refractory melanoma from studies MDX 020 or CA184-022 were treated with monotherapy 3 mg/kg of ipilimumab every 3 weeks for four doses and followed for at least 12 weeks. The overall rate of irAEs from CA184-022 (n=71), regardless of grade, was 65% (58% Grade 1 or 2 and 7% Grade 3 or 4). The most common events were skin-related (44% Grade 1 or 2 and 1% Grade 3 or 4), gastrointestinal, including diarrhea and enteritis (30% Grade 1 or 2 and 3% Grade 3 or 4). The formal safety analysis from the MDX-020 study (n=137) is published in Hodi et al., NEJM, 2010, however, no new safety signals were identified. The most recent ipilimumab Investigator Brochure (and addenda) should be consulted for the current details of safety.

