#### **1.3.5.a Drug-Related Deaths**

Based on reports from the safety data base as of June 30, 2009, there have been reports of death (approximately 1% [35/3800]), deemed by the investigator as possibly related to the administration of study drug. The most common cause of drug related deaths was GI perforation. Other causes included multiorgan failure, sepsis, hypotension, acidosis, Guillain-Barré-Syndrome and adult respiratory distress syndrome. The most recent Ipilimumab Investigator Brochure (and its addenda) should be consulted for the most current details of safety, including mortality data.

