Characteristic organ-specific inflammatory irAEs were reported with ipilimumab therapy, typically during induction therapy. IrAEs were mostly reversible within days to weeks following cessation of therapy or treatment with symptomatic therapy, corticosteroids or other anti-inflammatory agents, depending upon severity. Accumulated clinical experience resulted in

detailed toxicity management guidelines (also termed algorithms), by use of which irAEs can be effectively managed, especially when irAEs are recognized early and subjects are treated in a timely fashion. This can minimize the occurrence of irAE complications, such as GI perforation/colectomy or hepatic failure.

Since currently no cure for patients suffering from advanced melanoma is available and no drug ever has shown any survival benefit in prospective controlled randomized clinical phase III studies, ipilimumab at its 3mg/kg given four-times every 3 weeks is currently the best choice for melanoma patients who have failed systemic treatment in order to improve one- and two-year survival. Considering this background an irAE event rate of less than 25% grade 3-4 is highly acceptable.

In the context of the historical data which demonstrate a 2-year survival rate of approximately 8% to 18% in subjects with previously untreated advanced melanoma (Korn et al., 2008; Chapman et al., 1999; Middleton et al., 2000; Bedekian et al., 2006) 2-year survival rates for ipilimumab treated patients in clinical studies ranges from 29.81% to 41.78%.

The overall risk-benefit ratio for patients entering this protocol is therefore at least comparable to and possibly better than alternative options.

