### **3 STUDY DESIGN**

#### **3.1 Overall Study Design**

This is an open-label, multi-center, single-arm clinical phase II study to further characterize the efficacy and safety of ipilimumab (3 mg/kg iv every 3 weeks over 10 weeks) in patients with pretreated, metastatic and/or inoperable melanoma. .

The study will have one final analysis. The final analysis will occur 12 months after the last patient has been entered the clinical study. Prior to closure of the study, it will be ensured that survival data has been collected for each subject for 1 year following the subject's first treatment dose. A Safety Data Monitoring Committee (SDMC) will be responsible for reviewing all Grade 3-4 irAE on a regular basis. Based on its review the DMSB will provide the sponsor with recommendation regarding trial modification, continuation or termination.

**Figure 2 Study design**[figure not shown]

Tx = treatment with study medication

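### The 50% toxicity rule in section 6.3 divides by all treated patients, with no defined look and no minimum number, so during accrual it understates the toxicity rate and would fire late.

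*Protocol*

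**What the plan says.** Protocol section 6.3 opens with "The trial can be prematurely closed or suspended by the sponsor in following cases" and lists three triggers. The first is at least 50% "of treated patients present an AE" of grade III or higher with at least a possible relation to ipilimumab. The second is at least 20% with an unexpected related event that is not brought under control within 14 days of starting treatment for it. The third is any drug-related death not also attributed to progression. The section then states: "Patients who are already on treatment will be informed individually if stopping rules apply based on the interim safety analysis".

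Section 3.1 states "The study will have one final analysis". It also has a safety committee (SDMC) review grade 3-4 irAEs regularly, without an interval and without reference to 6.3. Section 6.2 treats anyone with one dose as evaluable for safety. Section 6.4.1 has adverse effects assessed continuously.

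On expected toxicity, section 1.4 says that "an irAE event rate of less than 25% grade 3-4 is highly acceptable". Section 1.3.4c reports irAEs at 3 mg/kg (n=71) as "65% (58% Grade 1 or 2 and 7% Grade 3 or 4"). Table 1 gives related AEs by grade for all doses and for 10 mg/kg.

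**The concern.** A percentage rule works only if three things are fixed: when it is read, on how many patients, and over what observation time. Section 6.3 fixes none of them and refers to an analysis the protocol does not contain.

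Accrual is fast, at up to 200 patients in 8-9 months, and toxicity takes time to appear. Section 1.3.5 puts first onset of endocrine irAEs at weeks 6 to 12. Dividing the events seen so far by everyone dosed so far gives a rate that is too low throughout accrual, which is when a pause would still protect patients. The trigger also lies well above the protocol's own background rates, and no reason is given. At stake is whether the rule can flag excess grade 3-4 toxicity while patients are still being enrolled. The primary endpoint is not affected.

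**Working it through.** The protocol states no look schedule, false-alarm rate or detection probability for the rule, so there is no figure of its own to reproduce.

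**1. Background for the same kind of event.** Table 1, related AEs of grade 3, 4 and 5. The 10 mg/kg grade rows add to the any-grade total (158 + 198 + 163 + 38 + 4 = 561), so grades can be summed.
- All doses: (617 + 127 + 20)/2901 = 764/2901 = 26.3%.
- 10 mg/kg: (163 + 38 + 4)/658 = 205/658 = 31.2%.
- Trigger relative to background: 50/26.3 = 1.9 and 50/31.2 = 1.6.

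**2. Chance of reaching 50% on complete data.** P(X ≥ n/2), X binomial(n, p), one look, every patient fully observed:

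| True rate | n = 100 | n = 200 |
|---|---|---|
| 35% | 0.1% | <0.01% |
| 40% | 2.7% | 0.3% |
| 45% | 18% | 8.9% |
| 50% | 54% | 53% |
| 60% | 98% | 99.8% |

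**3. Dilution when all treated patients are counted.** Assumptions: even accrual of 200 patients over 8.5 months (36.96 weeks), and onset of the first grade ≥3 event uniform between weeks a and b after first dose. The protocol gives no overall onset distribution, so three patterns are shown. With t weeks of accrual elapsed, the share of eventual events already visible is
- 1 − (a + b)/(2t) if t ≥ b;
- (t − a)²/(2(b − a)t) if a < t < b.

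Patient 100 is treated at t = 18.48 and patient 200 at t = 36.96. The eventual rate needed for an expected 50% is 0.5/share.

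| Onset (weeks) | Share at patient 100 | Rate needed | Share at patient 200 | Rate needed |
|---|---|---|---|---|
| 0-12 | 1 − 6/18.48 = 67.5% | 74% | 83.8% | 60% |
| 3-12 | 1 − 7.5/18.48 = 59.4% | 84% | 79.7% | 63% |
| 3-20 | 15.48²/(34 × 18.48) = 38.1% | 131%, unattainable | 68.9% | 73% |

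Counting patient by patient instead of with the smooth formula lowers each share by about half a point or less; the first two rates needed at patient 100 become 75% and 85%.

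**4. Effect of the denominator on firing.** Simulation with uniform random entry over 8.5 months, onset over weeks 0-12, weekly looks during accrual and at least 20 patients in the denominator. Chance that the 50% rule fires before accrual ends:

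| True rate | All treated | Observed ≥12 weeks |
|---|---|---|
| 25% | 0% | 0.9% |
| 40% | 0% | 27% |
| 50% | 3% | 85% |
| 60% | 64% | 99.9% |

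At a true 60%, the all-treated version fires after a median of about 150 patients have been treated; the observed version fires after about 89.

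**The case against.** A reader might infer that the rule cannot fire at clearly excessive toxicity. That is not so: on complete data it fires in about half of cases at a true 50% and nearly always at 60%. The unattainable result belongs to patient 100 under the 3-20 week pattern only. That pattern is also the least supported, since section 1.4 says irAEs typically arise during induction, whose last dose is in week 10.

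A reader might also set 50% directly against the 25% in section 1.4. That figure concerns grade 3-4 irAEs, a narrower class than related AEs of grade III or higher. It describes rates below 25% as acceptable and sets no upper limit. Table 1 is the fair comparison. The gap is smaller there, but remains.

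Nor is it fair to say that the rule would stop half of acceptable trials by chance. Checked on fully observed patients from the first one, it is crossed in 50% of trials at a true 25%. However, 1 − 0.75² = 44 of those 50 points come from an event in the first two patients, and a minimum of 20 brings the figure to 1.9%. This only shows that a minimum is needed.

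Other safeguards exist: the SDMC review, individual discontinuation criteria, the 20% rule and the death rule. With drug-related deaths at "approximately 1% [35/3800"]), the chance of at least one in 200 patients is 1 − (1 − 35/3800)^200 = 84%, or 75% at Table 1's 20/2901, if those rates carry over. The rule is also discretionary, and mention of an interim safety look beside one final analysis can be read as safety review versus efficacy analysis. Look timing could sit in a committee charter.

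These points lower the weight of the concern without removing it. The 20% rule covers only unexpected, uncontrolled events, and the death rule does not measure non-fatal toxicity. The SDMC reviews a different numerator and is not named in 6.3. The all-treated denominator is fixed in the protocol text itself, so it is not a detail left open.

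**Conclusion.** The concern holds in limited form. As written, the first rule in 6.3 has no defined look, no minimum number, and a denominator that includes patients with almost no observation time. During accrual it therefore understates toxicity: 38% to 67% of eventual events are visible at patient 100 and 69% to 84% at patient 200. The sizes rest on even accrual and assumed onset; the direction does not.

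Independently of dilution, the rule is very unlikely to respond to true rates of 35% to 40% (0.1% to 2.7% at n = 100), and the 50% trigger stands at 1.6 to 1.9 times the Table 1 background without justification. Apart from this rule, no stated rate trigger covers excess expected, non-fatal toxicity. The documents do not show that 50% is clinically wrong, and that is not claimed here.

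**What to change.** Reconcile sections 1.4, 3.1, 6.2 and 6.3, so that the interim safety analysis either is defined or is replaced by a reference to the SDMC reviews.

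Apply the percentage at stated SDMC reviews, with a minimum number, to patients whose first dose was at least a fixed safety period ago, or use a time-to-event estimate of the cumulative rate. Do not add early events from patients still inside that period unless their event-free peers are counted too. At patient 100 with a 12-week period, about 35 patients have completed it. At a true 25%, onset over weeks 0-12 would give 16.9 events among 35.1 + 8.1 patients, which reads as 39%; onset over weeks 3-12 would read as 36%.

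State the chance of firing at the rates the sponsor regards as acceptable and unacceptable. The sponsor should set or justify the clinical threshold and the length of the safety period.

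Cost: amendment wording, a few extra tabulations of data already collected, and possibly some additional review pauses.
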